## Abstract

**Introduction:**

The Western health system has primarily focused on a biomedical approach, prioritizing pharmaceutical and clinical treatments while overlooking the social, economic, psychological, and environmental dimensions of health. As a result, biomedical solutions have received disproportionate attention, while non-pharmacological, community-based interventions remain underutilized. The CAIR project seeks to address this imbalance by co-creating community-driven health initiatives in Municipal District 2 of Elche, Spain. This protocol describes the methodology for two population-based surveys conducted before and after the co-creation process to assess changes in key health and wellbeing indicators at the community level.

**Methods:**

A community-based participatory process will be implemented to engage residents in co-creating initiatives to promote health and wellbeing over a 3-year period (2026–2028). To evaluate population-level changes related to this co-creation process, a representative survey of 600 adult residents (≥18 years) in Municipal District 2 of Elche (Spain) will be conducted using stratified random sampling, administered both before and after the co-creation process. The survey will assess a set of selected indicators: health-related quality of life, critical health literacy, community capital, social capital and cohesion, and knowledge, attitudes, and practices related to antibiotic use. Sociodemographic data will also be collected to enable equity-focused analyses, including both relative and absolute differences between population groups. Findings from the baseline survey will inform the design and implementation of the co-created initiatives, particularly by highlighting equity considerations across population groups, while a before–after comparisons of survey indicators will be used to explore the effect of the co-created initiatives.

**Discussion:**

Overall, this study will generate population-level evidence on the effect of co-created initiatives in a low-income, culturally diverse urban setting in Spain. By documenting the contribution of co-creation to improve key health and wellbeing indicators, it will provide the evidence needed to further advance participatory approaches in public health.

**Trial registration:**

https://clinicaltrials.gov/ct2/show/NCT07237971, Research Registry Unique Identifying Number: NCT07237971.

## Introduction

1

The predominant approach in the Western health system continues focusing on a biomedical perspective on health, emphasizing individual-level solutions such as the application of drugs and treatments. This biomedical model overlooks the broader social, economic and environmental factors that influence health and wellbeing (1). It has also contributed to a growing trend toward medicalisation, in which health problems are interpreted as medical issues, ignoring their social and psychological dimensions (2). Moreover, biomedical solutions have received disproportionate attention, while non-pharmacological interventions, which have been shown to be effective, have tended to have limited implementation (3).

In a highly medicalised society with an increasing demand for healthcare, primary care services are particularly overburdened, limiting their full potential for health promotion or even impairing users' health in some cases. The efficiency of the system is called into question if users are forced to go to hospital emergency departments because they cannot have a timely appointment with their primary care physician (4). However, the problem goes beyond inefficiency: overburdened health services have a direct impact on health equity, widening the gap between the most and least well-off members of society. It has been shown that people with lower educational attainment endure longer waiting times and greater negative impact of shorter primary care visits (4, 5). Barriers to accessing health services affect the population unequally, with the poorest and most vulnerable groups being the most likely to experience these barriers (6).

Given the current context, the CAIR project (Co-creating Action to Improve Rationality in the health system) aims to stimulate changes in health system functioning and increase health equity by the co-creation of community-based initiatives to improve health and wellbeing in the Municipal District 2 of Elche, Spain. Co-creation, in this regard, is defined as a collaborative process that brings together different actors to design, implement and evaluate interventions aimed at improving population health. This approach includes the participation of diverse sectors, such as policy makers, health professionals, community organizations and citizens, working together to identify problems and develop and implement solutions in a participatory procedure. The process will incorporate an asset-based approach to health (7) by identifying and mobilizing community's existing assets. This approach can promote a sense of ownership and self-determination among community members, thereby strengthening their capacity to drive improvements in wellbeing and community health (8, 9).

Given its focus on medicalisation, the CAIR project targets three thematic domains in which overreliance on biomedical solutions and patterns of inappropriate or unnecessary treatment are especially evident. First, psychological wellbeing, with the aim of reducing unnecessary consumption of anxiolytics and antidepressants by strengthening community-level strategies that promote mental health and resilience. Second, cardiovascular health, where fostering preventive, community-based approaches can reduce dependence on medication to manage cardiovascular risk factors. Third, antimicrobial resistance, by promoting the rational use of antibiotics and supporting behaviors that help limit the emergence and spread of resistance. Together, these domains reflect key areas in which co-created, community-based initiatives may help counteract medicalisation while improving health, promoting equity, and reducing avoidable pressure on primary care services.

This protocol describes the population surveys that constitute a core component of the CAIR project. The surveys will be conducted twice during the project period—before and after the co-creation process—to capture changes over time in key indicators at the municipal district level. The surveys will generate quantitative evidence on the potential effects of moving from a predominantly biomedical model to one that embeds community participation and collective action in efforts to improve health.

Therefore, the aim of this study is to analyse changes in health-related quality of life, critical health literacy, social and community capital, and knowledge, attitudes, and practices regarding personal antibiotic use—and their implications for health equity—through population surveys conducted before and after the co-creation process in the Municipal District 2 of Elche, Spain.

## Methods and analysis

2

### Study design

2.1

The CAIR study applies a community-based participatory approach to engage citizens in co-creating initiatives to improve health and wellbeing. To evaluate their effect in the Municipal District, we will conduct representative population-based surveys before and after the three-year co-creation period (2026–2028). These surveys will measure health-related quality of life, critical health literacy, social and community capital, and knowledge, attitudes, and practices related to personal antibiotic use, alongside key sociodemographic characteristics to enable an equity-focused analysis. Baseline results will inform the co-creation process by identifying community needs, health status and health inequities, ensuring that initiatives are designed to address them effectively and fairly. Changes over time will be assessed by comparing indicators between surveys before and after the co-created intervention process, also estimating absolute and relative differences across population groups.

The broader CAIR project is registered on ClinicalTrials.gov (Identifier: NCT07237971). CAIR began on 1 October 2024 and will run for 5 years. Recruitment for the baseline survey started on 22 October 2025 and the post-intervention survey will be conducted in the final year, in 2029.

### Study setting

2.2

We will conduct a representative population-based survey among adult residents (≥18 years) in Municipal District 2 of Elche, Spain (Figure 1). This district includes the neighborhood of Carrús where resides 17.2% of the population of the city of Elche, with 36,065 residents in 2024. It is a diverse area, with 25.6% foreign-born residents, mainly from Morocco (6.2%), Colombia (5.3%), and Romania (3.1%) (10), as well as approximately 250 Roma families (11). The area shows levels of social vulnerability, with a high concentration of migrants and lower income levels. The Roma community faces structural discrimination and barriers to accessing education and employment, which negatively affect their wellbeing and opportunities (11).

**Figure 1 F1:**
[figure not shown]
Geographic distribution of census sections in the study area: Municipal District 2, Elche, Spain. According to the Elche City Council, this area is the Municipal District 2. In the National Institute of Statistics (INE) statistical classification, it is District 3.

We will work closely with the basic health councils of the two health centers that have a population residing in District 2 of Elche (Carrus Health Center and San Fermín Health Center). Basic Health Councils are established structures that promote citizen participation in health, bringing together representatives from the primary care team, local government, public health services, neighborhood associations, community organizations, and other relevant actors (12). Their role will be essential for mobilizing the local population and facilitating participation in the survey.

### Study population

2.3

We will recruit 600 participants using a stratified random sampling based on the 2021 census sections. The sampling will be stratified by census section, sex, age group to ensure its representativeness using population quotas from census data provided by Spain's National Statistics Institute (INE, Supplementary Table S1)(10). Furthermore we will apply an overall migrant quota of 25.6%. By using a stratified sampling, we ensure a representative sample of the neighbourhood's population, also in terms of representativeness of men and women across age groups for each of the different census sections that compound the District 2 of Elche. Furthermore, given that representativeness is a challenge for any population survey, targeted outreach through social media, local traditional media and community-based engagement activities will be employed to increase community awareness and improve response rates.

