#### Inclusion and exclusion criteria

2.3.1

Inclusion criteria:(a)People over 18 years of age who reside in the Municipal District 2 of Elche (Spain) (after providing informed consent to participate in the survey).Exclusion criteria:(a)People who cannot understand the questions or give informed consent due to language or cultural barriers, even after attempting to establish effective communication with the assistance of a cultural mediator.(b)People with physical or intellectual disabilities that prevent them from understanding the questions or signing the informed consent, despite reasonable efforts to facilitate communication.

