
For statistical analysis, we will use the latest version of Stata/SE (StataCorp, Texas, USA), and R: A language and environment for statistical computing (R Foundation for Statistical Computing, Vienna, Austria). The *p*-value obtained in the hypothesis tests performed will be described. Although we will use a *p*-value < 0.05 as a reference to identify statistically significant differences, this value should be interpreted with caution when subgroup stratified analyses with smaller sample sizes are conducted. The possibility of a type II error (false acceptance of the null hypothesis) will be considered, allowing for a more nuanced and contextualized interpretation of the results, thus avoiding the premature exclusion of potentially relevant trends in under-represented subgroups. No survey weights will be used in statistical analyses.

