For the surveys themselves, we also recognize potential challenges related to the underrepresentation of migrant populations, particularly those in more vulnerable situations. In this sense, such population groups—particularly migrants and racialised populations—are more likely to report poorer health outcomes and if they are underrepresented in the sample, the resulting estimates may be biased upwards, overstating the overall health status of the population. To mitigate this, the role of cultural mediators will be crucial to ensure culturally competent engagement and reduce barriers to facilitate the participation of such groups and Arabic-speaking individuals.

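### The 25.6% migrant quota matches a foreign-born share stated for residents with no age limit, yet it is applied to an adults-only, unweighted sample; its base should be confirmed or replaced with the adult share.

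*Protocol article*

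**What the plan says.** Section 2.2 (Study setting) defines the survey population: "We will conduct a representative population-based survey among adult residents (≥18 years) in Municipal District 2 of Elche, Spain". The eligibility criteria in section 2.3.1 also limit the sample to adults.

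Section 2.2 then describes the district as a whole, "with 36,065 residents in 2024. It is a diverse area, with 25.6% foreign-born residents". No age restriction is attached to either figure.

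Section 2.3 (Study population) sets quotas by census section, sex and age group from national statistics data and adds: "Furthermore we will apply an overall migrant quota of 25.6" per cent. It presents the result as a representative sample. Section 2.4 applies the same sampling design to 600 independent participants at each wave.

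Section 2.8 (Data analysis) ends with "No survey weights will be used in statistical analyses". The regression models adjust for migration status.

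**The concern.** The quota decides who is interviewed. It carries the same figure as a share that section 2.2 states for residents without an age limit, whereas the sample is drawn from adults. The two shares coincide only if minors and adults are foreign-born equally often. Children born in Spain to migrant parents are not foreign-born, so the share among minors may well be lower. In that case the adult share lies above 25.6% and the quota is too low.

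Three things would be affected: the claim of representativeness, the unweighted district means, and the size of the foreign-born subgroup, which matters because equity is a stated aim. The Discussion treats this type of error as consequential. Of migrants and racialised groups it says that "if they are underrepresented in the sample, the resulting estimates may be biased upwards, overstating the overall health status of the population". Model adjustment for migration status neither corrects an unweighted descriptive mean nor adds foreign-born respondents.

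**Working it through.** **1. Reproduce the plan's figure.** The quota in section 2.3 is 25.6% and the foreign-born share in section 2.2 is 25.6%, an exact match. On 600 participants: 0.256 × 600 = 153.6, about 154 people per wave. No share specific to adults appears anywhere in the article.

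**2. Adult share.** Let m be the share of residents who are minors and f the foreign-born share among minors. If 25.6% covers all ages, the adult share is

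a = (0.256 − m·f) / (1 − m), so that a − 0.256 = m(0.256 − f) / (1 − m).

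The sign depends only on whether f is below or above 25.6%. The article gives neither m nor f, so the values below are assumptions.

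| m | f | a | 600·a | difference from 153.6 |
|---|---|---|---|---|
| 15% | 20% | 0.226/0.85 = 26.6% | 159.5 | +5.9 |
| 18% | 10% | 0.238/0.82 = 29.0% | 174.1 | +20.5 |
| 20% | 5% | 0.246/0.80 = 30.75% | 184.5 | +30.9 |
| 18% | 25.6% | 25.6% | 153.6 | 0 |
| 18% | 30% | 0.202/0.82 = 24.6% | 147.8 | −5.8 |

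Widening m to 14–22%, with f at 5–20%, gives 26.5% to 31.4%.

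**3. Effect on the unweighted mean.** Shift = (a − 0.256) × gap in quality of life between native-born and foreign-born adults.

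- Assumed gap of 2 to 5 points: 0.0099 × 2 = 0.02 to 0.0515 × 5 = 0.26 points.
- Assumed gap of 0.2 to 0.5 SD: 0.0099 × 0.2 = 0.002 to 0.0515 × 0.5 = 0.026 SD.
- Standard error of a mean on 600: √(1.5/600) = 0.050 SD with the protocol's design effect of 1.5, or 1/√600 = 0.041 SD without it.

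The upper end is therefore about half a standard error (0.026/0.050), or 0.6 of one if the design effect is ignored.

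**4. Effect on subgroup precision.** In the middle case the foreign-born group would be 174 instead of 154. Confidence intervals scale by √(153.6/174.1) = 0.94, so they would be about 6% narrower.

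**5. Effect on the before–after contrast.** With the same quota in both waves, the error in the unweighted change is (a − 0.256) × (difference between the two groups in their change). The gap in level drops out, and the error is zero if both groups change equally. If only one wave's quota is moved, the full shift from step 3 enters the change.

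**The case against.** The strongest objections are these.

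- Section 2.2 does not say that children are included. The resident total and the percentage stand in separate sentences, and the supplementary quota table and the statistics source are not shown. This stands: all ages is the natural reading, supported by the section's own use of an explicit adult label for the survey population, but it is an inference.
- A range of f from 5% to 20% produces a shortfall by construction. This also stands, which is why the table includes the null and reversed cases.
- The effect is small and largely cancels in the main before–after analysis, which also adjusts for migration status. This stands. What remains is the descriptive level, the claim of representativeness and the subgroup size.
- Baseline recruitment began on 22 October 2025, so a new quota for 2029 alone would give the waves different migrant composition, contrary to section 2.4. This stands and governs the fix.

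A reader might go further and infer that foreign-born adults are certainly under-sampled, that the quota builds in the upward bias described in the Discussion, or that the estimated change is biased. The article supports none of these. The direction depends on figures it does not give. The Discussion's warning concerns hard-to-reach migrants in particular, and the protocol meets it with cultural mediators. A constant quota leaves the change largely intact.

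**Conclusion.** The point holds as a question about the base of one figure that the protocol fixes. A share stated without an age limit serves as the quota for an adult sample, nothing shows that it is the adult share, and the no-weights rule leaves any mismatch uncorrected in the district means.

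The size is modest. Assuming 15–20% minors and 5–20% of them foreign-born, 6 to 31 foreign-born adults per 600 would be missing in each wave. The unweighted mean would move by at most about half a standard error, given a gap of no more than 0.5 SD between groups. If f equals 25.6% there is no error, and above that foreign-born adults would be slightly over-sampled. The before–after comparison is largely protected as long as both waves use the same quota.

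**What to change.** 1. State the base of the 25.6%. If it is residents of all ages, replace it with the foreign-born share among residents aged 18 or over, from the national statistics source already used for the other quotas.
2. Do not change the composition of one wave only. Apply whichever quota is used identically at baseline and in 2029.
3. Where the baseline was filled at 25.6%, calibrate the district-level descriptive estimates of both waves to the adult share by migration status. Write this into section 2.8 as a stated exception to the no-weights rule, and report the before–after comparison on the same basis in both waves.

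The cost is one look-up, a small amount of extra analysis and a slight loss of precision. The approximate variance inflation from calibrating 25.6% to a is a²/0.256 + (1 − a)²/0.744, which is 1.006 at a = 29.0% and 1.014 at a = 30.75%. The sample size does not change. Calibration does not enlarge the foreign-born subgroup, so the precision loss in step 4 of the working would remain in a wave already filled at 25.6%.

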#### Inclusion and exclusion criteria

2.3.1

Inclusion criteria:(a)People over 18 years of age who reside in the Municipal District 2 of Elche (Spain) (after providing informed consent to participate in the survey).Exclusion criteria:(a)People who cannot understand the questions or give informed consent due to language or cultural barriers, even after attempting to establish effective communication with the assistance of a cultural mediator.(b)People with physical or intellectual disabilities that prevent them from understanding the questions or signing the informed consent, despite reasonable efforts to facilitate communication.

### Sample size estimation and selection criteria

2.4

The sample size has been calculated assuming that the prevalence of the variables of interest (e.g. proportion of individuals with poor health-related quality of life, proportion of individuals with limited critical health literacy etc.) does not exceed 30%, with an absolute precision of ± 5% and a confidence level of 95%. A design effect of 1.5 has been applied, following the recommendations of the World Health Organization's (WHO) STEPS guidelines (13) for complex designs. In addition, a rejection rate of up to 20% has been considered, implying the need to recruit at least 590 participants. The proposed inclusion of 600 participants also ensures the estimation of indicators for specific subgroups (such as by sex) with an absolute precision of close to ± 5%.

A before-and-after analysis will be conducted with 600 independent participants at each time point, selected using comparable samples and applying the same inclusion criteria and sampling design. This sample size is sufficient to detect significant differences in both our main outcome (i.e., health-related quality of life) and secondary variables. In the case of health-related quality of life, it allows us to identify absolute changes of around 10%, with a confidence level of 95% and a statistical power close to 80%. The exact power will depend on the initial prevalence of the indicator and the magnitude of the observed effect. Although the analysis of social inequalities may have lower power due to stratification by subgroups, we estimate that the sample size will be sufficient to identify relevant trends and significant differences in social inequalities in the studied sample.

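### The precision of close to ±5% promised for subgroups such as sex leaves out the plan's own design effect; on the stated inputs it is about ±6.4%

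*Protocol article*

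**What the plan says.** All the relevant statements are in the protocol article, mostly in section 2.4 (Sample size estimation and selection criteria).

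- The prevalence of the variables of interest is assumed to be one that "does not exceed 30"%. The target for the survey as a whole is ±"5% and a confidence level of 95"%.
- On the sampling design: "A design effect of 1.5 has been applied", citing guidance for complex designs.
- On refusals: "a rejection rate of up to 20% has been considered, implying the need to recruit at least 590 participants".
- On subgroups: the proposed 600 "ensures the estimation of indicators for specific subgroups (such as by sex) with an absolute precision of close to" ±5%. No separate prevalence, design effect or response assumption is given for subgroups.
- On the comparison over time: "A before-and-after analysis will be conducted with 600 independent participants at each time point".

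Section 2.3 (Study population) adds "We will recruit 600 participants using a stratified random sampling based on the 2021 census sections", with quotas by census section, sex and age group and an overall migrant quota of 25.6%.

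**The concern.** The section needs close to 500 respondents to reach ±5% for the district as a whole, and then promises nearly the same precision for each half of the sample. At a fixed prevalence and design effect, halving the number of respondents widens the interval by a factor of √2, so the two statements conflict.

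The figure matters because the survey is meant to support an equity analysis. Section 2.8 (Data analysis) stratifies health-related quality of life by sex, age group and other characteristics and uses the results to steer the co-creation discussions. Sex is a two-way split that should give two large groups, so whatever precision is quoted for it is close to the best that any subgroup will have. A reader who plans around ±5% will read more into a difference between groups than the data can carry.

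**Working it through.** **Inputs from section 2.4:** prevalence p = 0.30 (the stated maximum), half-width d = 0.05, 95% confidence (z = 1.96), design effect (DEFF) 1.5, rejection 20%, 600 participants per survey. **Assumption:** a 50:50 sex split, because the text shown does not give the split. That makes about 300 per sex if all 600 are interviewed.

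**1. Reproduce the plan's own figure.** n = z² p(1−p)/d² × DEFF.
- Simple random sample: 1.96² × 0.30 × 0.70 / 0.05² = 322.7.
- With the design effect: 322.7 × 1.5 = 484 respondents.
- With 20% rejection: 484 × 1.2 = 581, or 484/0.8 = about 606.

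The stated 590 lies between the two, so the overall calculation reproduces and the design effect is clearly part of it.

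**2. Precision of the whole sample.** Half-width = z √(DEFF × p(1−p)/n).
- 600 respondents: 1.96 × √(1.5 × 0.21/600) = 4.49%.
- 480 respondents: 1.96 × √(1.5 × 0.21/480) = 5.02%.

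**3. Precision per sex, same inputs.**

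| Respondents per sex | DEFF 1.5 | DEFF 1 |
|---|---|---|
| 300 (all 600 interviewed) | ±6.35% | ±5.19% |
| 240 (sensitivity: 480 of 600 usable) | ±7.10% | ±5.80% |

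For example, 1.96 × √(1.5 × 0.21/300) = 6.35%, which is also 4.49% × √2. The only cell near ±5% is the one with all 600 interviewed and no design effect. A finite-population correction changes little: with about 14,400 adults per sex (an assumption), ±6.35% becomes ±6.28%.

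**4. Where ±5% per sex would hold with DEFF 1.5.** Solve p(1−p) = 0.05² × 300/(1.5 × 1.96²) = 0.130, which gives p = 0.154. As a check, the half-width is ±4.95% at 15% and ±5.54% at 20%. At 30%, ±5% per sex would need about 484 respondents of each sex, or 968 in all.

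**5. A smaller subgroup, for scale.** The migrant quota gives 0.256 × 600 = about 154 people. With the same prevalence and design effect, the half-width is 1.96 × √(1.5 × 0.21/154) = 8.9%.

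**The case against.** Several points can be made for the plan.

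- **Thirty percent is a ceiling and 1.5 is a guideline default.** Both are true. At lower prevalence the intervals are narrower. Because sex cuts across the sampling routes, any clustering part of the design effect could also be smaller within a sex. With DEFF 1.25 (an illustration, not a figure from the plan), 300 per sex gives 1.96 × √(1.25 × 0.21/300) = ±5.8%. This is a good reason to let the authors state their subgroup assumptions. It does not rescue the sentence, which claims to ensure the precision, follows directly on the 30% and 1.5, and gives no other values.
- **The wording is hedged and the claim is a by-product.** The sentence sets no sample size and no test, and sections 2.4 and 2.8 both warn about subgroup power. Those warnings concern power and significance, not this precision figure, and 6.35 is 27% wider than 5.
- **The main outcome is summarised by a mean.** A half-width for a proportion does not apply to it. However, section 2.4 frames its indicators as proportions, including the proportion with poor quality of life, and the claim has to be judged in those terms.

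Two stronger readings are tempting and are not supported.

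- **That the rejection allowance was forgotten, so the design delivers ±7.1%.** Recruitment to quotas, and the reference to 600 independent participants at each time point, favour reading 600 as people interviewed. The ±7.1% is a sensitivity figure only.
- **That the power claim fails as well.** It does not. With 600 completed interviews per wave and DEFF 1.5, the effective number is 600/1.5 = 400. A fall from 30% to 20% gives 0.10/√((0.21 + 0.16)/400) − 1.96 = 1.33, or 91% power. A rise from 30% to 40% gives 0.10/√((0.21 + 0.24)/400) − 1.96 = 1.02, or 85%. With only 480 usable (effective 320), the fall still has 84% and the rise has 76%. The plan claims about 80% and says that the exact value depends on the initial prevalence.

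**Conclusion.** The subgroup precision is wrong as written. On the plan's stated inputs it is about ±6.4% per sex rather than close to ±5%, a shortfall of roughly 1.4 percentage points in half-width. This rests on 30% prevalence, a design effect of 1.5, an even sex split and all 600 being interviewed. An uneven split would make the smaller group less precise. The error does not depend on how the 20% rejection is read, because the ±6.4% already counts every one of the 600.

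The finding goes no further than that figure. The overall sample size reproduces and the power statement stands. This is a modest correction to one sentence, worth making because the plan's equity analysis relies on subgroup estimates.

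**What to change.** In section 2.4, do one of the following:

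- restate the sex-specific precision as about ±6.4% at 30% prevalence with the design effect of 1.5, noting about ±7.1% if only 480 of the 600 were usable; or
- keep close to ±5% and state the subgroup prevalence and design effect that produce it.

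In either case, add that smaller subgroups, such as the migrant group, will be estimated less precisely.

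As a clarification only, it would help to say that 600 means completed interviews per wave. At 20% refusal that means approaching about 600/0.8 = 750 people.

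The cost is one or two sentences and a slightly less favourable figure. The sample size, design and analysis do not change.
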